##### Telehealth

Local families unable to attend the clinic in person will be offered their MDT assessment using telehealth with assistance from the therapist or clinic nurse. The HINE assessment will be arranged to be completed by the PĒPI ARC therapist either at the time of the telehealth appointment or at another time convenient for the family. They can also contact the Hub/PĒPI ARC team via email and phone at any time within the study time to request support or answer questions.

#### Infants and families living outside of the Wellington region

##### Virtual hub

The virtual PĒPI ARC Hub will offer flexible support for families, paediatricians, and therapists to aid the timely completion of early detection assessments (Table 2). The Hub will be able to assist with the interpretation of specific assessments, triangulation of the results, CP diagnosis, and communicating the assessment outcomes to the families. If an infant receives a high risk of CP/CP diagnosis, additional information relating to early intervention, monitoring of comorbidities and complications of CP, parental support, and parent information about CP will be offered.

### Usual care for infants at high risk of neurodevelopmental impairment admitted to the Wellington NICU

#### All high-risk infants

•MRI is routinely done only for infants with hypoxic ischaemic encephalopathy (HIE) Grades 2 and 3.•Routinely referred to the neonatal therapist of the unit and on an as-needed basis to other allied health.•Whilst staff try to implement the CPCN Recommendations, early GMA assessments are not always completed due to medical status and availability of the infant.

#### Infants from the Wellington region

•Followed by the discharge facilitator team throughout their NICU admission and for a period after discharge. This team provides emotional and practical support, prepares families for discharge, organises family meetings, ensures follow-up appointments are made, and assists families once home with feeding support including nasogastric tube feeding and assessment of infants between clinic visits.•Referred to a visting neonatal therapist on discharge for neurodevelopmental surveillance, who may assist with GMA and HINE. The onset of this service and the length of follow-up time may vary.•Followed-up by their hospital neonatologist, variable number of appointments, and length of follow-up.•Follow-up with SLT, dietician, and other health professionals only if referred prior to discharge.•No social work follow-up.•No MDT clinics.

#### Infants from outside the Wellington region

•There is no service similar to the discharge facilitator team for infants whose families reside outside of Wellington during their NICU stay.•Referred for paediatric and CDS for follow-up and neurodevelopmental surveillance on discharge from NICU. Variation between regions for the onset of services, length of follow-up time, and number of appointments and assessments (26).•Three regional centres have clinicians that trained in GMAs, and a further three regional centres send GMA videos to the Wellington GMA team for scoring.•All regions have therapists trained in HINE. The timing of HINE assessments varies.•An electronic report with individual GMA scores and an impression of outcome based on the trajectory at 3–4 months CGA is forwarded by the Wellington GMA team to a local therapist following the evaluation of scores.•No MDT clinics.•It is important to acknowledge that during the study timeline, changes in “usual care” may occur.

### Outcome measures and data collection

Feasibility will be assessed by using the outcomes, measures, and data capture summarised in Table 4, from March 2023 to September 2024. Data will be directly entered into REDCap (hosted by the Wellington Hospital and MRINZ infrastructures), which will only be accessed by the members of the research team involved in the data entry and analysis. Due to the scope and minimal risks associated with the study, there is no formal data monitoring committee. Interim data monitoring will be conducted at a 6-month review of survey feedback, and auditing of trial conduct will be completed by the primary investigator and study and clinical coordinators on a fortnightly basis. Quantitative data collection tools, surveys for families, health professionals and the PĒPI ARC MDT team, participant information, consent form, and data management plan are available on Open Science Framework (OSF, DOI: https://doi.org/10.1101/2023.10.31.23297869).

**Table 4 T4:** Summary of outcomes, data capture, and measures/approaches for PĒPI ARC.

Objective	Data capture	Measures/approaches
Implementation		
1. To determine to what extent the early CP detection assessments can be implemented equitably to infants with newborn detectable risks admitted to a level 3 NICU	• Demographic information for infants eligible for the CPCN Recommendations pathway (NICU discharge data) • PĒPI ARC clinic notes and medical records	The proportion of infants completing the neuroimaging, GMA, and HINE (as per CPCN Recommendations), with outcomes grouped and compared by: • Region of residence • Ethnicity (Māori, Pasifika, non- Māori/Pasifika)
2. To evaluate if the fidelity of the CPCN recommendations can be maintained, including diagnostic assessments completed, communication with families, and related referrals	• Infant medical records/PĒPI ARC clinic notes • Records for assessments • Referral data • Questionnaire—health professionals • Semi-structured interviews with health professionals and families	The total number and proportion of diagnostic tests completed/not completed (i.e., not grouped by region or ethnicity). Of participants with a high risk of CP/CP detected: • The number of participants whose parents were informed of the diagnosis, and the age and acceptability of communication • The timing of therapist review post high-risk CP diagnosis • The timing of referral for surveillance of comorbidities and medical complications as indicated • The number of families receiving information about practical and emotional support
Acceptability		
3. To evaluate the acceptability of the PĒPI ARC Hub model of care by families and health professionals	• Questionnaires—families, health professionals, and the PĒPI ARC team. • Semi-structured interviews with families and health professionals	Data will be interpreted according to those families and health professionals involved in the Hub who were from Wellington compared with other regional centres
Demand		
4. To determine the demand for the PĒPI ARC Hub among families and health professionals	• PĒPI ARC clinic notes/statistics • Infant medical records (virtual Hub) • Communications with the PĒPI ARC team: logged as part of an audit trail. The full audit trail will be reviewed at the end of the study in combination with questionnaire data	Using the number of infants and families approached to take part in PĒPI ARC: • The proportion of families who consent to the study • The proportion of infants who attend the clinic • The proportion of infants who complete regional follow-up appointments with paediatricians/therapists • The proportion of families that chose to use telehealth • The number and profiles of health professionals accessing the Hub for support • The type of support requested by families and health professionals
Limited efficacy		
5. To evaluate if the PĒPI ARC Hub model reduces the age of CP diagnosis	• PĒPI ARC clinic notes • Infant medical records	• The average age when a preliminary high-risk CP or CP diagnosis was made and age (/rate) of CP confirmation
6. To explore the experiences around communication and information sharing between families and health professionals	• Semi-structured interviews with families and health professionals	• Qualitative analysis of participant experience

NICU, neonatal intensive care unit; CP, cerebral palsy; GMA, General Movements Assessment; HINE, Hammersmith Infant Neurological Examination.

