### PĒPI ARC

The PĒPI ARC Hub applies a modified multidisciplinary team (MDT) approach to health service delivery and care for infants with detectable risk factors for CP who are admitted to a tertiary neonatal intensive care unit (NICU). The Hub aims to develop a Māori-centered relationship model of care with Whanaungatanga (connectedness) and Whakawhanaungatanga (building relationships) at its core (15), incorporating the key interrelated dimensions of Māori holistic healthcare including wairua (spiritual), whānau (extended family network), hinengaro (the mind, emotion), and tinana (physical). Whānau represents the collective way Māori operate. People do not exist in isolation but include a person's immediate and extended family. PĒPI ARC embraces the view that at the centre of care is the patient (i.e., infant) and their extended family and seeks to (1) build relationships and connections through the journey of infants in NICU, their transition to home, and follow-up support in their community (16) and (2) to coordinate care and minimise the burden for families in attending multiple appointments with different health professionals.

The Hub provides three functions:
1.A face-to-face clinic for infants and their families living in Wellington2.Support to families and infants who reside in other regions to access GMA and HINE assessments, by working in close partnership with the families, their local doctors, and therapists3.Partnership with, and support for, local and regional health professionals to use early detection strategies and communication with families

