### Hypotheses

**H1**: Equivalent levels of infants who meet the criteria will undergo assessments with CP-specific diagnostic tools outlined in the CPCN Recommendations, independent of region of residence or ethnicity.

**H2**: Whānau and health professionals will find the PĒPI ARC Hub model of care acceptable (over the acceptability constructs).

**H3**: The demand will be high with infants who meet the criteria choosing to enroll in the PĒPI ARC study over standard care.

**H4**: More than 34% of infants with CP will be diagnosed before 12 months of corrected gestation age (CGA) and >17% before the age of 6 months CGA.

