### Study design and setting

The PĒPI ARC study is a prospective, non-randomised, feasibility study that uses a mixed methods approach to evaluate the previously outlined domains of feasibility. The study will run from March 2023 to September 2024, with the primary time point being at the completion of the PĒPI ARC Hub trial period. The study setting will be a regional Hub based in Wellington to allow follow-up of eligible infants who received care at the Wellington NICU. The PĒPI ARC Hub will be delivered using two components: a community-based, multidisciplinary face-to-face diagnostic clinic in Wellington and a virtual Hub to support regional CP-specific neurodevelopmental follow-up, education, and information sharing and foster relationships among the Wellington team, local community, and regional child development services (CDS) and paediatricians.

The Wellington NICU is a tertiary unit that provides perinatal and surgical care for infants from Wellington and seven regional referral centres from half of the North Island and the top of the South Island of NZ. The unit cares for a third of all infants admitted to a tertiary NICU in NZ. It is estimated that between 100 and 120 infants per year will fit the criteria for the CPCN Recommendations pathway, of which approximately 30% live in the Wellington area (21) (i.e., to be invited to attend the in-person clinic), and the remainder will receive follow-up in their local regions (supported by the PĒPI ARC team through telehealth).

For the Wellington NICU catchment area, data from the NZ CP Register (2009–2020) showed that 17% of infants received a diagnosis of CP before 6 months of age and 34% before 12 months (22).

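### Demand measures in Table 4: dividing clinic attendance and regional follow-up by everyone approached caps them at about 30% and 70%, even with full uptake

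*Protocol article*

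**What the plan says.** The demand row of Table 4 (Objective 4, under Outcome measures and data collection) opens with the base "Using the number of infants and families approached to take part in PĒPI ARC". Four proportions follow:

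- for consent, "The proportion of families who consent to the study";
- for use of the face-to-face service, "The proportion of infants who attend the clinic";
- for care outside Wellington, "The proportion of infants who complete regional follow-up appointments with paediatricians/therapists";
- and for remote access, "The proportion of families that chose to use telehealth".

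Two further items in the same cell, on health professionals using the Hub and on the type of support requested, are not proportions. No other base is given for any of the four. The Clinic/medical data section names an attendance rate for clinics among the descriptive statistics but does not define it.

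Elsewhere the article says who can use each service. The first function listed for the Hub is "A face-to-face clinic for infants and their families living in Wellington". Study design and setting estimates 100 to 120 eligible infants per year, "of which approximately 30% live in the Wellington area", and says the remainder are followed up in their own regions. Eligibility covers both groups, so both are approached. The Discussion states that families who decline are not followed.

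**The concern.** A proportion describes uptake only if everyone in the denominator could have appeared in the numerator. About 70% of eligible infants live outside Wellington and are not among those to be invited to the in-person clinic. About 30% live in Wellington and are not the group meant for regional follow-up. Dividing both counts by everyone approached makes each figure a product of residence, consent and attendance, and the first of these says nothing about demand.

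The treatment of decliners adds to this. They stay in the denominator but are not followed, so the calculation treats them as not having completed follow-up. Under usual care, out-of-region infants are also referred for paediatric and child development follow-up, so some decliners may attend regional appointments that the study never sees.

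The secondary objective is to determine demand among both local and regional families. Read at face value, a fully attended clinic would look like a service that most families passed over.

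**Working it through.** **Plan's own figure.** The article states no attendance target, demand threshold or sample size calculation, so there is nothing to reproduce. The check is for the largest value each measure can take under the written base.

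**Inputs**
- N, infants approached: 100 to 120, taking the yearly estimate of eligible infants in Study design and setting and assuming all are approached. N cancels from every ratio below.
- w, Wellington share: about 0.30 (same section). Regional share: 1 − w = 0.70.
- Assumption: approached families have the same residence mix as eligible infants. I vary w from 0.25 to 0.35 because the article gives it only as approximate.
- Consent c = 0.80 and attendance or completion a = 0.90 are illustrations and are not in the article.

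**Step 1: ceilings (c = a = 1)**

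Maximum clinic attendance = wN / N = w. Maximum regional follow-up = (1 − w)N / N = 1 − w.

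| w | Clinic ceiling | Regional ceiling |
|---|---|---|
| 0.25 | 25% | 75% |
| 0.30 | 30% (30/100 or 36/120) | 70% (70/100 or 84/120) |
| 0.35 | 35% | 65% |

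**Step 2: a good but imperfect result (w = 0.30, c = 0.80, a = 0.90)**

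- Clinic attendance over everyone approached: w × c × a = 0.30 × 0.80 × 0.90 = 21.6%.
- Over Wellington infants approached: c × a = 0.80 × 0.90 = 72%.
- Over Wellington infants enrolled: a = 90%.

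The same clinic is reported as 21.6% or 90% depending only on the base. For regional follow-up at the same rates, the written base gives 0.70 × 0.80 × 0.90 = 50.4%, against 90% of enrolled regional infants.

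**Step 3: the other two proportions**

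- Consent: every approached family can consent or decline, so the base fits the measure and there is no cap.
- Telehealth: it supports regional infants and is also the alternative for local families who cannot attend in person. Residence does not cap it, but one pooled figure mixes two different uses. A local family that switches to telehealth also lowers clinic attendance without showing less demand.

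**The case against.** **The lead-in may be only a loose heading.** It also stands over two items that cannot be divided by families approached, so it could mean no more than starting from those approached and reporting the flow. A sensible analyst would read a clinic attendance rate as attended over invited, and an analysis plan that is not shown may say so. This stands as a possible reading, and it limits how firmly one can predict what will be reported. It does not remove the point: the families-approached base is the only one the article states, and nothing in it supplies another.

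**The measures are descriptive and secondary.** There is no test and no demand threshold, and a reader who knows that the clinic is for Wellington families could correct for it. This also stands, and it limits the weight of the point.

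**Stronger readings that the article does not support**
- A reader might infer that H3 would be judged on capped figures. H3 says "The demand will be high with infants who meet the criteria choosing to enroll in the PĒPI ARC study over standard care", which is about enrolment. The consent proportion addresses it, and residence does not cap that proportion.
- A reader might infer that consent over families approached inflates uptake because eligible families never approached drop out. Consented over approached is a conventional rate and suits H3, since a family can choose the study over usual care only once it has been invited. Nothing in the article suggests that approach will be incomplete, and any figure for such inflation would rest on an invented approach rate.
- A reader might infer that a planned comparison of local with regional demand is spoiled. Table 4 groups by region for Objective 1 and compares Wellington with other centres for Objective 3, but specifies no such comparison for Objective 4.

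**Conclusion.** The point holds for two of the four demand proportions. Followed as written, Table 4 cannot report clinic attendance above about 30% or regional follow-up above about 70%, however well the Hub is taken up. Families who decline and are not followed also count as non-completers. The ceilings rest on the article's approximate 30% Wellington share and on approached families having the same residence mix as eligible infants; a share of 25% to 35% moves them to 25–35% and 65–75%.

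The harm is to the interpretation of two descriptive measures of a secondary objective. H3's consent rate, the primary objective and the error rates are unaffected. It is worth correcting because the stated rule would understate demand among both groups that the objective names, and the correction is cheap.

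**What to change.** Replace the single lead-in for Objective 4 with a base for each proportion:

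- **Consent:** families approached, as now.
- **Clinic attendance:** enrolled infants living in the Wellington region.
- **Completion of regional follow-up appointments:** enrolled infants living in the referral regions.
- **Telehealth use:** enrolled families, shown separately for Wellington and for the regions.

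Keep the outcomes as defined. No new composite of Hub contacts is needed. Nor is a telehealth rate among those offered it, since the article does not list offers as a recorded item. The items on health professionals and on support requested stay as counts and descriptions.

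The cost is a change to the wording of Table 4. It uses residence and enrolment data that the study already collects.

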MRI, Magnetic Resonance Imaging; GMA, General Movements Assessment; HINE, Hammersmith Infant Neurological Examination; CP, cerebral palsy; CGA, corrected gestational age; ICFQ, The Feeding Matters Infant and Child Feeding Questionnaire.

^a^
Scored by the GMA team or at least two senior assessors (inter-rater reliability of the assessors will be established beyond 80% prior to PĒPI ARC clinic appointments beginning). If consensus on scoring is not reached, the GMA will be reviewed independently by a third assessor, including referral to expert assessors if needed until consensus is reached.

**Table 3 T3:** Process plan for communicating outcomes to families/health professionals.

If an infant is assessed to be at low risk of CP: • Verbal and written feedback will be provided to the family and local team. • The infant will be discharged from the PĒPI ARC clinic to usual care.
If the assessments are inconclusive: • Explanation of inconclusive findings will be provided verbally and documented in clinic letters provided to the family and neonatologist/therapist. • The infant will be seen in the PĒPI ARC clinic for further assessment in 2–4 weeks for a repeat clinical examination.
If an infant is diagnosed with CP or high-risk of CP: • The family will be offered a follow-up appointment with the PĒPI ARC team including the social worker within 1–2 weeks’ time (face to face or telehealth based on their preference) to answer any questions and receive more information. All ongoing care will be with their local neonatologist/paediatrician and therapist. • Screening for comorbidities will occur, and genetic testing will be offered. Support and follow-up referral will be made. • Information about the diagnosis of high-risk of CP or CP, the referrals made, and advice about ongoing follow-up and monitoring will be provided to the family of the infant, primary neonatologist/paediatrician, therapist, and GP.

CP, cerebral palsy; GP, general practitioner.

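### Table 4 reports telehealth choice as one proportion of all families approached, which does not fit a design where residence largely sets the route to telehealth

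*Protocol article*

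**What the plan says.** In the protocol article, Table 4 (Outcome measures and data collection) gives the measures for Objective 4, Demand. They are introduced by "Using the number of infants and families approached to take part in PĒPI ARC", and one of them is "The proportion of families that chose to use telehealth". Separate items cover consent, clinic attendance and completed regional follow-up. No split by region is stated for this objective, although the Secondary objectives section says that demand concerns both local and regional families.

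Telehealth appears in three roles elsewhere in the article:

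- **Regional families.** Study design and setting says that "the remainder will receive follow-up in their local regions (supported by the PĒPI ARC team through telehealth". The Virtual hub section describes the support in looser terms: "The virtual PĒPI ARC Hub will offer flexible support for families, paediatricians, and therapists".
- **Wellington families.** The Telehealth section says: "Local families unable to attend the clinic in person will be offered their MDT assessment using telehealth".
- **After a CP or high-risk result.** Table 3 offers a follow-up appointment, "face to face or telehealth based on their preference".

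Table 4 does not say which of these roles the measure counts.

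**The concern.** A proportion of families who *chose* telehealth measures demand only if the families in the denominator had that choice. Here most did not have the same one. For regional families telehealth is the planned means of support. For Wellington families it is an alternative when in-person attendance is not possible. Only the Table 3 appointment is described as a matter of preference, and it is limited to families with a CP or high-risk result.

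The Discussion presents delivery by two routes as a strength of the study, so readers will probably use this figure to judge the virtual route. Pooled over everyone approached, it cannot show whether families wanted telehealth, and its size depends heavily on which role is counted.

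The adjacent clinic-attendance measure has the same difficulty. Only Wellington infants are to be invited to the in-person clinic, yet the base is all infants and families approached. The text also does not say whether an MDT assessment done by telehealth counts as attending.

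**Working it through.** The article gives no telehealth proportion to reproduce. The check is what the measure can show on its stated base.

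**Inputs from the article**

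- Eligible infants: "It is estimated that between 100 and 120 infants per year will fit the criteria for the CPCN Recommendations pathway".
- Wellington share: "of which approximately 30% live in the Wellington area", so w = 0.30. That is 30 to 36 infants (0.30 × 100 to 0.30 × 120), leaving 70 to 84 regional infants.
- Base: infants and families approached.

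**Assumptions (not in the article)**

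- c: share of approached families who consent, taken as equal in both groups.
- t: share of enrolled Wellington families assessed by telehealth.
- u: share of enrolled regional families who use telehealth.
- One family per infant, and those approached split 30/70 like those eligible.

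**Formulas**

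- Narrow reading (Wellington alternative only) = c × 0.30 × t.
- Broad reading (any telehealth) = c × (0.70 × u + 0.30 × t).
- Difference = 0.70 × u × c, whatever t is.

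**Ceiling of the narrow reading.** With c = t = 1 it is 0.30. Even if every Wellington family used telehealth, the figure could not pass about 30%.

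**Illustrations with t = 10% to 30%**

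| c | u | Narrow | Broad | Difference |
|---|---|---|---|---|
| 1.0 | 1.0 | 3–9% | 73–79% | 70 points |
| 1.0 | 0.5 | 3–9% | 38–44% | 35 points |
| 0.8 | 1.0 | 2.4–7.2% | 58.4–63.2% | 56 points |
| 0.6 | 0.5 | 1.8–5.4% | 22.8–26.4% | 21 points |

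In the first row, regional families contribute 70 of the 73 to 79 points. In the last they contribute 0.6 × 0.70 × 0.5 = 21 of the 22.8 to 26.4 points. In every row the broad figure is driven mainly by residence and hardly moves with t.

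**Table 3 reading.** Only families with a CP or high-risk result are offered this choice. The article gives no expected number of them, so no size is computed. Over all families approached, the proportion would depend on how many infants have such a result as well as on preference.

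**Clinic attendance on the same base.** The ceiling is 0.30 × c, so about 30% at full consent. If 10% to 30% of Wellington families had the assessment by telehealth and this were not counted as attendance, the figure would be 0.30 × 0.90 = 27% down to 0.30 × 0.70 = 21%. All Wellington families would nevertheless have received the Hub assessment.

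**The case against.** The strongest reply is that nothing here is contradictory. The regional and Wellington descriptions concern different families and are compatible. Telehealth is a heading only under the Wellington section, regional follow-up has its own item in Table 4, and the verb *chose* fits poorly with a planned regional route. The narrow reading is therefore the natural one. The Wellington alternative is also offered, so a family may decline it. In addition, the article is condensed, and it says that the data collection tools and data management plan are posted separately. They may define the event.

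Much of this stands. A reader might infer that the protocol contradicts itself about telehealth, but it does not. A reader might also take the first row of the table as what the trial's data would show. The article does not support that: it gives no consent rate and no telehealth use in either group. The Virtual hub section describes flexible support offered to clinicians as well as families, so use by every regional family is not stated.

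The mismatch of measure and base does not go away. It lies in what Table 4 states, not in something left to another document. Even on the natural narrow reading, about 70% of the denominator never faces that choice, which caps the figure near 30%.

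**Conclusion.** The point holds as a minor one. On the base that Table 4 states, none of the three readings measures families' demand for telehealth. The Wellington reading is capped near 30%, the broad reading mainly reflects residence, and the Table 3 reading concerns a subgroup whose size is not given. The 30% cap rests on the article's own 30/70 split and on approached families following it. The gap between the narrow and broad readings, at most 70 points and 35 at half regional use with full consent, rests also on the assumed rates.

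Two stronger conclusions are tempting. One is that Wellington families assessed by telehealth are scored as not using the Hub. The article does not say so; it leaves open whether such an assessment counts as attendance, and telehealth is listed as a separate item. The other is that the test of H3 is compromised. H3 concerns enrolment over standard care, which the consent proportion addresses. The telehealth item is descriptive, with no threshold or test, and the primary objective does not depend on it.

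**What to change.** Replace the telehealth bullet in Table 4 with three items, each over its own denominator:

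1. **Enrolled Wellington infants:** Hub MDT assessment in person, by telehealth, or not done, with in person plus telehealth reported as uptake. This also settles how such an assessment relates to the clinic-attendance item.
2. **Enrolled regional families:** any direct telehealth contact between the family and the Hub, labelled as use and not as choice.
3. **Families offered the Table 3 follow-up appointment:** the proportion choosing telehealth.

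The cost is a wording change and slightly more tabulation. Table 4 already lists the clinic notes, the medical records for the virtual Hub and the communication log as sources; the mode of each appointment or contact would have to be extracted from them. The denominators become small: about 30 to 36 Wellington infants at full enrolment, and an unknown, probably smaller, number for item 3. Counts should therefore be shown beside percentages. If the posted data collection tools already define the event, a reference to that definition and the split by region would be enough.
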